## Abstract

**Background:**

Generalised anxiety disorder (GAD) is a chronic and debilitating condition characterised by high co-morbidity. Alongside pharmacological treatment, cognitive behavioural therapy (CBT) is an established psychological therapy for GAD. Its effectiveness is limited, however, with only an estimated 50% of clients presenting in the non-clinical range after a course of treatment. Furthermore, not all clients prefer CBT as a psychological therapy. Recently, emotion-focused therapy (EFT) was developed for GAD and was tested in an open trial with promising results.

**Methods/design:**

The present research project is a feasibility testing randomised controlled trial (RCT) that compares the efficacy of EFT with an established treatment for GAD, CBT. Sixty clients presenting in a primary care psychology/counselling service will be randomly assigned to one of two conditions: EFT or CBT. Outcomes will be assessed using several measures (Generalised Anxiety Disorder-7, Generalised Anxiety Disorder Severity Scale, Patient Health Questionnaire-9, and Clinical Outcome in Routine Evaluation – Outcome Measure). Clients will be assessed prior to and at the end of therapy, as well as at 6-month follow-up. On the basis of findings from the initial open EFT trial with regard to the optimal length of therapy, it is proposed that therapy last between 16 and 20 sessions.

**Discussion:**

This study aims to test the feasibility of a full comparison RCT. It will test subject recruitment, therapist adherence to manualised treatment, and client retention rates. It will also provide estimates of comparative outcomes that can inform power calculations for a definitive trial.

**Trial registration:**

ISRCTN Registry, ISRCTN52689081. Registered on 24 October 2017.

**Electronic supplementary material:**

The online version of this article (10.1186/s13063-018-2892-0) contains supplementary material, which is available to authorized users.

## Background

Generalised anxiety disorder (GAD) is a common anxiety disorder [1]. Its 1-year prevalence is around 3%, whereas its lifetime prevalence is around 5% [2–5]. Furthermore, co-morbidity is high, with almost 60% of individuals diagnosed with GAD also meeting diagnostic criteria for depression and an additional anxiety disorder [6]. Co-morbidity with personality disorders is also very high, particularly avoidant and dependent personality disorders [7]. People with GAD experience significant impairment in quality of life comparable to that of people with depression [8, 9]. GAD represents a significant cost to society owing to disability, decreased work productivity and increased use of health care services [5].

Current guidelines recommend that GAD be treated by medication and/or a psychological therapy (cf. National Institute for Health and Care Excellence [NICE] [10]). Among psychological treatments for GAD, various forms of cognitive behavioural therapy (CBT) are the most recognised treatments [11]. CBTs for GAD have been shown to be more effective than wait-list comparisons [12–14]. CBT treatments for GAD include a number of common interventions; however, there is significant variation among them [11]. Broadly speaking, CBT models of treatment variously use a number of the following components/interventions: psychoeducation about worry, cognitive restructuring of beliefs relating to worry, problem solving, monitoring and shaping of the worry process, relaxation training, exposure, and behavioural experiments, and others [11].

Although the efficacy of CBTs is well studied, not all clients benefit from CBT. Less than 50% of clients recover by the end of the treatment, and long-term follow-up data is sparse [13, 15]. A Cochrane review of psychological therapies for GAD recommends that “further studies examining non-CBT models are required to inform health care policy on the most appropriate forms of psychological therapy in treating GAD” [14]. Furthermore, research on patient preferences for therapies for other disorders shows that some patients prefer other psychological therapies to CBT [16]. The development of new treatments for GAD may also show that the effectiveness of new treatments may differ when compared with CBT, as has been shown, for example, in the case of depression [17]. These arguments led a group of researchers to adapt emotion-focused therapy (EFT) for the treatment of GAD [18, 19].

EFT [20, 21] is a research-informed therapy that focuses on (1) increasing awareness of adaptive and maladaptive emotions, (2) enhancing emotion regulation, (3) transforming maladaptive emotions and (4) reflecting on adaptive emotions [22]. EFT is an empirically supported treatment for major depressive disorder [17, 23] and is also extensively studied for complex trauma [24]. In comparison with CBT for depression, EFT showed comparable results with a slight advantage for EFT in the domain of interpersonal functioning [17]. EFT is also currently being adapted for other mental health disorders, such as social anxiety, where the central problems lie in maladaptive emotional processing [25–28]. Because GAD is understood to be caused by difficulties in emotional processing (e.g., an incapacity to tolerate difficult emotions, combined with a tendency to avoid such difficult emotions) [11, 29], a therapy such as EFT that focuses on the processing and transformation of painful emotions is theoretically a good match for GAD difficulties [18]. Furthermore, EFT also focuses on the overcoming of emotional avoidance, a central feature of GAD.

A group of researchers, led by the lead author of the present article, developed EFT for GAD [18, 19] and tested it in an open trial with promising results [30]. The present project should further contribute to the exploration of EFT as a viable alternative to CBT in the treatment of GAD. The feasibility study should establish the relative efficacy of EFT in comparison to CBT as an established treatment.

### Objectives

The overall aim of the project is to contribute to the planning of a definitive non-inferiority trial that would establish the relative efficacy of EFT in comparison to CBT as an established treatment. The present project will provide first-comparison data that, if suggesting comparable or better outcomes, should help to plan a definitive non-inferiority trial. It will test recruitment, adherence, and retention rates, as well as provide estimates of comparative outcomes that can be used to inform power calculations for a definitive non-inferiority trial.

## Methods/design

### Trial design and setting

The design of the study is a randomised controlled trial (RCT) with two active parallel interventions (EFT and CBT). This reported version of the protocol conforms to the Standard Protocol Items: Recommendations for Interventional Trials (SPIRIT) guidelines. (For a copy of the SPIRIT checklist, *see* Additional file 1).

Participants will be recruited from a national public health primary care service in Ireland. The Health Service Executive (HSE) provides public health services across Ireland, and the HSE’s Counselling in Primary Care (CIPC) service provides counselling to clients who present to primary care with mental health difficulties such as anxiety and depression. CIPC was established by the HSE on a nationwide basis in 2013 following the commitment outlined in the Programme for Government strategy [31] to implement Vision for Change [32] and improve access to psychological therapy.

### Participants/clients

Participants (*n* = 60) will be adults (aged ≥ 18 years) who are medical card holders (i.e., entitled to free public health care) referred by their general practitioner (GP) to the CIPC counselling service for anxiety issues. Clients will be screened for GAD using the Generalised Anxiety Disorder 7-item scale (GAD-7) [33]. If a GAD diagnosis is suspected (the client’s GAD-7 score must be ≥ 11), a comprehensive assessment will follow using the Structured Clinical Interview for DSM-5, Research Version (SCID-5-RV) [34]. Clients who meet the criteria for GAD as a principal diagnosis will be assigned to one of the trial arms. To participate in the study, participants must consent to the conditions of the study (e.g., audio recording of sessions, attendance at pre- and post-therapy assessment sessions). Individuals taking psychotropic medication must be stabilised on that medication for 6 weeks prior to commencing therapy (cf. [29]). Clients receiving psychotropic medication will have to show, with their physician’s approval, a willingness to maintain this stability in medication use during the period of therapy (medication use will be monitored during the trial). Participants must also give consent for their GP to be contacted in relation to their participation in the study. Exclusion criteria are concurrent psychological treatment, suicide risk (as defined by a score other than 0 on item 16 of the Clinical Outcome in Routine Evaluation – Outcome Measure [CORE-OM] [35]: “I have made plans to end my life”), risk of harm to others (as defined by a score other than 0 on item 6 of the CORE-OM: “I have been physically violent to others”), substance abuse, psychosis, and organic brain syndrome as determined by the SCID-5-RV. For further information on intake assessment, *see below*.

### Therapists

Therapists will be trained in both EFT for GAD and CBT for GAD. All therapists will randomly deliver both conditions (*see below*), thus random allocation will be nested within therapists. Therapists will be HSE CIPC employees already working routinely within the CIPC service. Optimally all therapists will be counselling psychologists; it is planned that all therapists will have prior training in both CBT and EFT (*see below*). It is envisaged that the interventions will be delivered by at least six therapists. However, given the likelihood that therapists in CIPC may change jobs over the life of the trial (especially in the context of wider changes in recruitment practice within the HSE), we intend to train more therapists than needed to account for possible attrition.

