### Randomisation

Because the organisational structure of CIPC means that it would not always be possible to randomise between therapists (e.g., often only one therapist works in a particular location), the decision was made to randomise within therapists. [name], a member of the research team with no allegiance to either intervention and no involvement in the delivery of either training or supervision, will generate the allocation sequence using an online randomiser. A random sequence (of numbers 1 and 2, corresponding to EFT or CBT) will be generated for each therapist, who will be identified by code and not by name. After SCID-5 assessment (*see below*), and after allocation to a therapist (*see* the next section on patient consent process and assessment), a member of the research team (the trial manager) will contact [name] and request the assignment (either EFT or CBT) for the next participant for the therapist in question.

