### Sample size

A sample size of 60 participants was determined (using G*Power) [45] on the basis of the comparison between the two active treatments and pre-post within-group comparison. We used a minimum meaningful comparison (moderate effect size; *f* = 0.25) that is used in assessing difference between two treatments (cf. Shapiro [46]), with statistical power of 0.80 and alpha level of 0.05.

We expect that the study is likely to detect change over time within the two active treatments (the pre-post change should be large). It is envisaged, however, that the sample size may be too small to find any difference between the active treatments (often the differences between active treatments are rather small). Because the present project is a feasibility study, exploratory use of the initial comparison data should help in planning a definite non-inferiority trial that could be developed as phase 2 of the present study, with further participants recruited to the two active interventions on the basis of an estimate of the numbers needed to determine definite evaluation.

Practically speaking, there should be a sufficient number of referrals. Annual referral numbers for CIPC Dublin North-East, where the study is hosted, is estimated at approximately 2000 clients, with at least 25% of individuals referred for anxiety problems. Because we will be recruiting over a 2-year period, we anticipate no issue with recruiting 60+ participants from a prospective pool of 1000 clients.

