### Statistical methods

The main analysis will be performed under the direction of [name]. The main analysis will be run as intention-to-treat analysis (within- and between-group comparisons at 16 weeks, the end of treatment, and at 6-month follow-up) as well as per-protocol analysis (which will exclude participants that had fewer than eight sessions; i.e., half of the expected length of the treatment).

Primary (GAD-7) and secondary (GADSS, PHQ-9 and CORE) outcomes will be analysed using repeated-measures analysis of variance for the two active conditions at the end of treatment, at 16 weeks, and at the 6-month follow-up. Analyses will be based on the intention-to-treat sample. Effects will be tested at the 0.05 level. The magnitude of the within-group effects of each of the interventions (Cohen’s *d*) will be calculated. The magnitude of between-group effects will be established as well. Analysis will also be conducted to determine the proportion of participants who evinced clinically significant change and reliable improvement [47] at the end of the treatment, at 16 weeks, and at 6-month follow-up for the two active treatments on the GAD-7.

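### Allocation is randomised within therapist, but the named analysis has no therapist term: the standard error of the EFT-CBT difference can be off in either direction, modestly, and no therapist variance is produced for the definitive trial

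*Protocol article*

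**What the plan says.** All of this is in the protocol article.

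- **Therapists section:** "All therapists will randomly deliver both conditions", and "thus random allocation will be nested within therapists". At least six therapists are expected, and extra therapists are to be trained against attrition.
- **Therapist training and supervision section:** ten therapists were trained and two have left, which leaves eight.
- **Randomisation section:** because some locations have a single therapist, "the decision was made to randomise within therapists". Each therapist gets a separate random sequence. The section does not say whether the sequences are blocked.
- **Statistical methods section:** primary and secondary outcomes are to be analysed by "repeated-measures analysis of variance for the two active conditions" across the assessment times. "Effects will be tested at the 0.05 level". No therapist factor, stratum or random effect is named.
- **Sample size section:** 60 participants, with no allowance for therapists.
- **Data management section:** the trial code identifies the participant's therapist.
- **Objectives section:** the comparative estimates are meant to feed the power calculation of a definitive non-inferiority trial.

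**The concern.** Therapist is the stratum within which participants are randomised, and it is crossed with arm. An analysis with condition and time alone treats 60 participants as independent, although they share about 6 to 8 therapists. Two components of variation are then mishandled, and they pull in opposite directions.

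- **Therapist main effect** (some therapists get better results whatever they deliver). Where arms are balanced within therapist, this cancels out of the arm difference, but the simple analysis leaves it in the residual. The standard error is then too large.
- **Therapist-by-treatment variation** (a therapist is better at one therapy than the other). This does not cancel. Left out, it makes the standard error too small for conclusions about therapists in general. It is plausible here because each therapy has its own training and supervisors.

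The second matter is planning. The article looks ahead to a definitive trial in a service of 280 therapists. Its sample size will depend on therapist variance, and no analysis described in the article estimates that variance.

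**Working it through.** **The plan's own figure.** The Sample size section states: "A sample size of 60 participants was determined (using G*Power"), with "moderate effect size; *f* = 0.25", "with statistical power of 0.80 and alpha level of 0.05". An ordinary two-group comparison at f = 0.25 needs 128 in total and has 48% power at 60. About 60 comes out only with a repeated-measures correlation that the article does not give (for example, the interaction with two measures and correlation 0.1 gives 60). That is a separate matter and nothing below depends on it. What matters here is that the stated inputs include no therapist component.

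**Inputs.** From the article: N = 60, and k = 6 (planned minimum) or k = 8 (remaining) therapists. With equal caseloads and 1:1 allocation (assumed), clients per therapist per arm are m = 60/(2k) = 5 or 3.75. Also assumed, since the article gives no figure: therapist-by-treatment share of variance ρ_tb = 0.02 to 0.05, and therapist main-effect share ρ_b = 0.05 to 0.10. Total variance is set to 1, and one outcome time is considered.

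**Balanced within therapist.**

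- True variance of the arm difference: 2ρ_tb/k + 2(1 − ρ_b − ρ_tb)/(km)
- Variance assumed when therapist is ignored: 2/(km)
- Ratio: 1 + (m − 1)ρ_tb − ρ_b

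| k | ρ_b | ρ_tb = 0.02 | ρ_tb = 0.05 |
|---|---|---|---|
| 6 | 0.05 | 1 + 0.08 − 0.05 = 1.03 | 1 + 0.20 − 0.05 = 1.15 |
| 6 | 0.10 | 0.98 | 1.10 |
| 8 | 0.05 | 1 + 0.055 − 0.05 = 1.005 | 1 + 0.1375 − 0.05 = 1.0875 |
| 8 | 0.10 | 0.955 | 1.0375 |

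The 0.955 cell needs 3.75 clients per therapist per arm. With whole caseloads of 7 or 8 and sequences blocked in pairs, simulation (20,000 runs) gives 0.98 for that cell. It puts the top cell nearer 1.18, because the estimated residual variance falls slightly below the total. I quote about 0.98 to 1.15.

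**Unblocked sequences.** Same set-up, with a fair coin for each client and 20,000 runs per cell. Entries are the variance ratio and the type I error of the therapist-ignoring test at nominal 0.05:

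| k | ρ_b | ρ_tb = 0.02 | ρ_tb = 0.05 |
|---|---|---|---|
| 6 | 0.05 | 1.11; 0.062 | 1.23; 0.075 |
| 6 | 0.10 | 1.11; 0.063 | 1.24; 0.078 |
| 8 | 0.05 | 1.08; 0.060 | 1.16; 0.069 |
| 8 | 0.10 | 1.05; 0.057 | 1.17; 0.071 |

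Allowing for simulation error, that is about 1.04 to 1.25, and 0.055 to 0.08. With ρ_tb = 0 the error stays at about 0.05. A fixed therapist term does not remove the inflation: at ρ_tb = 0.05 and ρ_b = 0.05, simulated error was still about 0.08 (k = 6) and 0.07 (k = 8).

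**Price of using therapist-by-treatment as the error term** (ρ_b = ρ_tb = 0.05; 95% half-width for d, balanced allocation):

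- Therapist ignored: √(2/30) = 0.258; × 2.00 (58 df) = 0.52
- k = 6: √(0.10/6 + 1.80/30) = 0.277; × 2.57 (5 df) = 0.71
- k = 8: √(0.10/8 + 1.80/30) = 0.269; × 2.36 (7 df) = 0.64

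Most of the widening comes from the few degrees of freedom.

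**Precision of the component.** At a true ρ_tb of 0.05, its 95% interval runs from below 0 to about 0.58 (k = 6) or 0.52 (k = 8).

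**Relevance to the definitive trial (illustration only).** The article gives no margin. Assume d = 0.3, one-sided 0.025 and 80% power: 2(1.96 + 0.84)²/0.3² gives 175 per arm. With 10 clients per therapist per arm and no offset for ρ_b, the multiplier is 1 + 9ρ_tb. That gives 175 × 1.18 = 207 at ρ_tb = 0.02 and 175 × 1.45 = 254 at ρ_tb = 0.05.

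**The case against.** The strongest reply is that a journal article names its method in one sentence and leaves model terms to a fuller document. Therapist is not excluded, and the within-therapist allocation is openly disclosed. This has some force, but the article itself makes therapist the basis of allocation and then commits to a named model without it. That is a mismatch between two stated choices, not merely an omitted detail.

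Other parts of the reply stand and limit the point:

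- A reader might infer that the planned standard error is necessarily too small and the 0.05 test anti-conservative. The article does not support that. It neither says whether sequences are blocked nor gives any variance share. With balanced sequences and a small therapist-by-treatment share, the ratio is close to or below 1.
- A reader might infer that a random therapist-by-arm effect must be in the primary model. That goes too far. Conclusions limited to the trial's own therapists are legitimate, the Sample size section calls the use of the comparison data exploratory, and with 6 to 8 therapists the component may be estimated at zero.
- A reader might infer that the definitive trial can never have an estimate. The trial code records the therapist, so the data will exist; only the analysis is not planned. Even when done, it will not fix a sample size by itself.
- A reader might take the word nested in the Therapists section as an error for crossed. It describes allocation carried out within each therapist, and the same sentence says that therapists deliver both conditions. It needs no change.

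**Conclusion.** The point holds in limited form. The named analysis does not follow the within-therapist randomisation, its standard error for the EFT-CBT difference can be wrong in either direction, and no described analysis estimates therapist variance for the definitive trial.

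The effect is modest. At the top of the unblocked range, the true standard error is about 12% above the assumed one (√1.25 = 1.12). At the bottom of the balanced range, it is about 1% below (√0.98 = 0.99). These sizes rest on assumed variance shares, equal caseloads and 6 to 8 therapists. The between-arm test is not confirmatory, so the planning loss matters at least as much as the error rate.

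**What to change.** In the Statistical methods section:

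1. Replace the repeated-measures ANOVA with a mixed model for repeated measures that includes a random therapist intercept. This brings the randomisation stratum into the primary analysis.
2. Add a sensitivity analysis with a random therapist-by-arm effect and small-sample (Kenward-Roger) degrees of freedom, for conclusions beyond these therapists. The random intercept alone does not cover that component.
3. Report both therapist variance components with confidence intervals, and use them as a sensitivity range, not as point values, when planning the definitive trial.

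The cost is a little more analysis work and no new data collection. With 6 to 8 therapists the components will be very imprecise or estimated at zero, and the interval in the sensitivity analysis will be wider (half-width for d of about 0.64 to 0.71 against 0.52 under the assumptions above).

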### Interventions

#### Emotion-focused therapy for GAD

The EFT intervention follows a recently developed model [18, 19] based on a research project led by the lead author of this article, [name] [30]. The EFT model uses a specific case conceptualisation which postulates that rather than being avoidant of emotional experience or of emotional processing in general (as typically proposed in CBT models), clients struggle to cope with specific triggers which evoke in them specific chronic maladaptive painful feelings (e.g., sadness/loneliness, shame, and primary fear/terror). It is these triggers that the client then avoids (through emotional and behavioural avoidance, one expression of which is excessive worrying). In the context of these triggers, the client attempts to cope with his or her own painful feelings, often through negative self-treatment. It is further postulated that, contrary to mainstream CBT theories, change will be facilitated not through emotional habituation to difficult triggers, but rather through the restructuring and transformation of problematic emotion schemes through a sequence of emotional processing steps (cf. [18, 19, 36, 37]).

The model of transformation assumes that the client is first facilitated to tolerate specific painful feelings; that he or she is then facilitated to articulate the unmet needs implicit in these painful feelings; and finally that, in doing so, he or she is helped to transform these painful feelings through the generation of adaptive emotions such as compassion and healthy protective anger. The therapy focuses on (1) a firm case conceptualisation, (2) the provision of a soothing relationship, (3) the overcoming of avoidance (worry) through experiential tasks which highlight both the cost of worry and the cost of obstructing the meeting of own needs (thereby leading to a resolve to fight the worry), and (4) the transformation of chronic dreaded painful feelings through experiential tasks that generate adaptive emotions (e.g., compassion and protective anger) in response to chronic emotional pain and the unmet needs embedded in that pain.

Therapy will last 16–20 sessions. Therapists will be instructed to finish therapy at session 16, but it will be at their discretion to clinically judge whether therapy should be prolonged to a maximum of 20 sessions. This flexible ending is based on learning from the initial project [30], in which some clients needed more than the initially anticipated 16–20 sessions (in some instances up to 24 sessions). Routine practice in CIPC allows for an extension of therapy, provided there are good clinical reasons to do so. We propose that therapists continue to use the same criteria as currently used within CIPC when deciding whether to extend therapy; that is, (1) the client continues to be clinically distressed (e.g., the therapist can use a formal assessment such as the GAD-7, which is collected as part of the study), and (2) the client expresses an explicit wish to continue with therapy for up to another 4 sessions. The number of sessions will be monitored, and these data will form part of a cost-effectiveness analysis between the two active interventions.

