It is anticipated that the first therapy session will typically take place 1 week after the assessment appointment with the research team. Post-treatment assessments will take place at week 16 (i.e., as close as possible to 16 calendar weeks from the date of the first session) and 6 months after 16 weeks (as close as possible to 42 calendar weeks from the date of the first session). In addition, when participants finish therapy outside the range of 16 ± 2 weeks (i.e., ≤ 13 weeks or ≥ 19 weeks), an additional assessment will be carried out post-therapy (i.e., as close as possible to the date of the last session). Sixteen-week, post-therapy and 6-month follow-up assessments will consist of administering the GAD-7, GADSS, CORE-OM and PHQ-9. In addition, the Counselling in Primary Care Client Satisfaction Survey (CIPC-CSS), which is routinely administered to all CIPC clients at the end of therapy, will be administered (*see below* for a description of measures).

If, during the course of the treatment, any client’s clinical condition suggests another course of treatment (e.g., further assessment, hospitalisation, acute risk management), this will be provided as per typical CIPC service guidelines. [name] (CIPC Director of Counselling) and the counselling co-ordinators who conduct regular clinical supervision will oversee any clinical issues arising. It has been agreed with CIPC that if, during follow-up assessment, any participant presents at risk or in significant distress, the research team will contact both CIPC and the participant’s GP to inform them of same.

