#### Primary outcome

The severity of GAD symptoms will be measured at pre-therapy, post-therapy (16 weeks; but also after the last session in cases where the last session falls outside the range of 16 ± 2 weeks) and at 6-month follow-up, using the GAD-7 as the primary outcome measure.

The GAD-7 [33] is a seven-item self-report questionnaire assessing GAD symptoms over the preceding 2 weeks. Using the threshold score of 10, the GAD-7 has been reported to have a sensitivity of 89% and a specificity of 82% for GAD; it has also been reported as having good reliability, as well as criterion, construct, factorial, and procedural validity [33].

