### Assessor training

Assessments will be conducted by a doctoral-level counselling psychologist and by psychology graduates (typically at master’s level or studying at master’s level) under the supervision of the doctoral-level psychologist. SCID-5-RV, SCID-5-PD and GADSS assessments will be audio-recorded and archived for subsequent evaluation of adherence to appropriate testing conditions. Assessors conducting post-therapy assessments will be blind to the condition the client was in.

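### The therapist may use the study GAD-7 when deciding on sessions 17 to 20, and the study GAD-7 due near that point is the self-reported week-16 primary outcome; the two uses should be separated

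*Protocol article*

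**What the plan says.** Under Interventions (Emotion-focused therapy for GAD), the article fixes the usual end of therapy and leaves extension to the therapist: "Therapists will be instructed to finish therapy at session 16, but it will be at their discretion to clinically judge whether therapy should be prolonged", up to 20 sessions. Two criteria are carried over from routine service practice. The first is that the client is still clinically distressed, and here the article adds that "the therapist can use a formal assessment such as the GAD-7, which is collected as part of the study". The second is that "the client expresses an explicit wish to continue with therapy for up to another 4 sessions". The CBT section gives the same discretion and the same maximum, without repeating the criteria.

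The Primary outcome section describes assessment "using the GAD-7 as the primary outcome measure", and says that the instrument "is a seven-item self-report questionnaire assessing GAD symptoms over the preceding 2 weeks". On timing, Patient consent process and assessment says: "Post-treatment assessments will take place at week 16", counted in calendar weeks from the first session. A further assessment is added when therapy ends at 13 weeks or earlier, or at 19 weeks or later, and there is a 6-month follow-up.

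The Therapists section has every therapist delivering both conditions, so the therapist knows the arm. Blinding is stated only in Assessor training: "Assessors conducting post-therapy assessments will be blind to the condition the client was in".

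**The concern.** A self-report outcome is best collected when nothing for the respondent depends on the answer. Here the article names the study's own primary measure as possible evidence for a decision on up to four more sessions. That decision lies with the therapist, who knows the arm, and needs the wish of the client, who completes the scale. Assessor blinding does not protect a self-report score against this.

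What is at stake are the week-16 estimates: within-arm Cohen's d, the proportions with reliable and clinically significant change, and the between-arm GAD-7 difference (Statistical methods). The Objectives section says that the comparative outcome estimates will inform power calculations for a definitive non-inferiority trial.

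**Working it through.** The plan gives no figure on this point, so there is none to reproduce. The check has three parts.

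**1. Which GAD-7 could be meant.** The text lists study GAD-7 assessments at pre-therapy, at week 16, after the last session if that falls outside 16 ± 2 weeks, and at 6-month follow-up. It describes no separate mid-therapy administration (the schedule figure is not shown). Of those listed, only the week-16 score falls near the decision about session 17. No section separates the outcome score from the one used for extension, or withholds it from the therapist.

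**2. Timing.** Session frequency is not stated. Weekly sessions are an assumption, consistent with the 16 ± 2 week window. Session *k* then falls *k* − 1 weeks after session 1:

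- session 16: 16 − 1 = 15 weeks
- session 20: 20 − 1 = 19 weeks
- outcome assessment: as near as possible to 16 weeks

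On a strict weekly schedule, session 16 comes about one week before the assessment. One missed week brings them together, and further missed weeks put the assessment first. A client extended to session 20 ends at about week 19 and so qualifies for the additional end-of-therapy assessment.

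**3. Size, on assumed inputs only.** Let *s*₁ and *s*₂ be the shares in each arm who score higher because they want more sessions, and *c* the inflation in GAD-7 points. The mean of arm *i* rises by *c* × *sᵢ*, and the arm difference shifts by *c* × (*s*₁ − *s*₂). Every share, *c* and the SD of 5 are assumptions; the article gives none of them.

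| Shares | *c* (points) | Shift in arm difference (points) | In SD (÷ 5) |
|---|---|---|---|
| 30% / 30% | 1 to 3 | 0 | 0 |
| 40% / 20% | 1 to 3 | 0.2 to 0.6 | 0.04 to 0.12 |
| 50% / 30% | 2 to 3 | 0.4 to 0.6 | 0.08 to 0.12 |

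For the within-arm effect, the mean rises by 0.30 × 2 = 0.6 points at the low end and 0.50 × 3 = 1.5 points at the high end. That is 0.12 to 0.30 SD, in the direction of less improvement. It does not cancel when both arms are affected equally: at 30% in each arm and 2 to 3 points, each mean still rises by 0.6 to 0.9 points.

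For scale, the Discussion section puts differences between psychotherapies often at 0 to 0.2 of Cohen's *d*. A shift of 0.08 to 0.12 SD is 40% to 60% of the upper end of that range.

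**The case against.** The case on the other side is substantial, and much of it stands.

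- **The score does not decide.** The GAD-7 is offered as an example of what the therapist can use. There is no threshold, no form is required, and the client's wish is a separate criterion. A reader might infer that a high score is needed to obtain more sessions; the text does not say so.
- **The order of events may not fit.** On strict weekly sessions the week-16 score arrives after session 16. This stands as a limit, but the two dates are close enough that ordinary slippage joins them.
- **Clients may not know.** Nothing says they are told that the research score bears on extension. Without that knowledge they have no incentive to score higher.
- **No difference between arms is shown.** The same therapists work in both arms under the same discretion and cap. A reader might infer differential demand because the flexible ending was based on the EFT open trial, where some clients needed more sessions than planned. That trial gives no comparison with CBT, so the inference is unsupported.
- **Assessor blinding is not shown to be broken.** A reader might see a channel between the assessment team and the therapist. The article does not say that week-16 scores are passed on, and a score going from assessor to therapist would not reveal the arm to the assessor.
- **Other data limit the damage.** The 6-month GAD-7, the additional assessment for late finishers, and the GADSS (an interview rating with blinded post-therapy assessors) are not tied to the decision in this way. Session numbers are monitored, so a difference in extension by arm would be visible.

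It can also be said that how scores are released is operational detail left to the full protocol. That would answer a complaint of silence. Here the article itself says that the study measure may be used for the decision, and that statement needs to be reconciled with its role as primary outcome.

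**Conclusion.** The point holds as a stated dual use of the primary outcome measure, with a modest and conditional claim of harm. The article allows a therapist who knows the arm to draw on the study GAD-7 for the extension decision, and the scheduled score nearest that decision is the week-16 primary outcome.

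The effect on within-arm change and reliable-change rates depends on clients knowing of the link and responding to it. The effect on the arm contrast also requires extension-seeking to differ by arm: it is nil at equal shares and about 0.1 SD under the 30% versus 50% illustration. These figures rest on assumed shares, inflation and SD, and show what could happen rather than what is expected. The documents do not support a claim that the week-16 comparison is biased. What they support is an inexpensive protection of the primary outcome.

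**What to change.** Reconcile the extension paragraph under Emotion-focused therapy for GAD with the Primary outcome section and Patient consent process and assessment:

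- State that the week-16 GAD-7 collected by the research team is not released to therapists for the extension decision. The existing arrangement for reporting risk or significant distress found at assessment is excepted.
- Tell clients this before they complete the form.
- State that any formal measure a therapist uses for that decision is given separately in routine care and kept out of the outcome data set. That measure may still be a GAD-7; only the research administration is set aside.

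The extension criteria are left as they are. The cost is a few sentences in the protocol and the assessment script. Some clients will complete a second short form near session 16 and may try to answer the two consistently, so the separation reduces the link without removing it entirely.
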